### Outcome Measures

#### Primary Outcome Measure: Incidence of ADRs

The incidence of ADRs is the primary outcome measure, and we will identify factors that contributed to the occurrence of ADRs. The incidence of ADR will be primarily categorized in accordance with the criteria proposed by the Committee of International Organization of Medical Sciences: very common (≥10%), common (1%-10%, including 1%), occasional (0.1%-1%, including 0.1%), rare (0.01%-0.1%, including 0.01%), and very rare (<0.01%) [28], as well as according to the classification of ADR symptoms by the World Health Organization (WHO) [29]. The WHO classification of organs and systems involved in ADRs will also be referenced [30]. The incidence characteristics and regional distribution will be subsequently analyzed, while concurrently investigating the influencing factors (Table 2).

**Table 2 table2:** Centralized monitoring results of Pudilan Xiaoyan oral liquid in the registered hospitals.

Monitoring result	Description
Categorization	The ADR^a^ was categorized based on general, novel, and severe classifications The classification was based on the organs and systems affected by the ADR The symptoms of the ADR were classified
ADR incidence	The specific event features of each ADR included the incidence rates of various categories and whether they are infrequent or exceptionally rare
Pedogenic properties	Occurrence characteristics of ADRs specific to each category
Geographical distribution	The distribution of ADRs is primarily observed in North China, Central China, South China Each region exhibits distinct characteristics of ADRs
Influencing factors	Days of medication, age, drug combination, etc

^a^ADR: adverse drug reaction.

#### Secondary Outcome Measures

##### The Ratio of Patients Whose Body Temperature Returned to the Normal Range

The cases of body temperature normalization and the duration for achieving normal body temperature within a 3-day period will be documented. The body temperature will be recorded prior to medication, on the first day after medication, and on the second and third days after medication. Daily measurements will be conducted by professional nurses using mercury thermometers. The time of normal body temperature restoration is defined as when the body temperature drops below 37.3 °C after the initial medication administration, with no recurrence observed within a 24-hour period. Thus, the ratio of normalization represented the percentage of cases in which individuals return to a normal body temperature within the total number of cases in the group.

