**Inclusion criteria**
Patients with upper respiratory tract infection (URTI) who are administeredPudilan Xiaoyanoral liquid; the diagnostic criteria for URTI are based on the disease code J06.900 of theInternational Classification of Diseases, 11th RevisionAged between 18 and 80 years

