**Exclusion criteria**
Lactating women, pregnant women, those planning to become pregnant, patients with psychiatric conditions, and others

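### The temperature-normalisation ratio divides by all cases although fever is not required at entry, and first normal readings on day 3 cannot be checked against the 24-hour rule

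*Protocol article*

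**What the plan says.** All of this is in the protocol article.

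- **Ratio.** Under Secondary Outcome Measures, the section on the ratio of patients whose temperature returned to normal defines the result as "the percentage of cases in which individuals return to a normal body temperature within the total number of cases in the group".
- **Normalisation.** The same section dates it to "when the body temperature drops below 37.3 °C after the initial medication administration", "with no recurrence observed within a 24-hour period".
- **Readings.** "The body temperature will be recorded prior to medication, on the first day after medication, and on the second and third days after medication". It adds: "Daily measurements will be conducted by professional nurses using mercury thermometers".
- **Window.** The section states that "the duration for achieving normal body temperature within a 3-day period will be documented". The closing sentence of the section on change in renal function instead gives 7 days as the time frame for all four outcome items.
- **Entry.** The inclusion criteria admit "Patients with upper respiratory tract infection (URTI) who are" given PDL and aged 18 to 80. The exclusions are "Lactating women, pregnant women, those planning to become pregnant, patients with psychiatric conditions, and others". Neither list mentions body temperature.

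**The concern.** A patient whose temperature is already below 37.3 °C before the first dose has nothing to return from. Such a patient can never enter the numerator but is counted in the denominator. The percentage then mixes two quantities: how many patients had fever at entry, and how many of those recovered. A reader will take it as the second alone. Two hospitals with the same recovery rate but different febrile shares would report different ratios; the article does not say whether the shares differ among its 17 hospitals.

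The second problem is smaller. A first normal reading on day 1 or day 2 is followed by another listed reading a day later, so the no-recurrence condition can be tested. A first normal reading on day 3 is followed by none, so the same condition is applied unevenly within one ratio.

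**Working it through.** **Plan's own figure.** None exists for this outcome: no expected ratio, sample size or precision is stated. The only calculation in the article is the rule of three for ADRs, on which this point does not depend.

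**Step 1: who is in the denominator.** The inclusion criteria set no temperature threshold. The listed exclusions do not remove afebrile patients; the closing words of that list are open-ended, but nothing ties them to temperature. The Introduction describes URTI as covering several syndromes, the common cold among them, without requiring fever. The Abstract repeats the outcome with no fever restriction. No febrile subgroup is defined anywhere in the article.

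**Step 2: effect on the ratio.** Inputs, both assumed because the article gives neither:

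- f = share of patients at or above 37.3 °C before dosing, 20% to 100%
- r = share of those febrile patients who normalise, 80%, with 70% and 90% as alternatives

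Afebrile patients add nothing to the numerator, so:

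- ratio over all cases = f × r
- ratio over patients febrile before dosing = r

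| f | Febrile among the planned 10,000 | Normalised at r = 80% | Ratio over all cases | Ratio over febrile cases |
|---|---|---|---|---|
| 20% | 2,000 | 1,600 | 16% | 80% |
| 40% | 4,000 | 3,200 | 32% | 80% |
| 60% | 6,000 | 4,800 | 48% | 80% |
| 80% | 8,000 | 6,400 | 64% | 80% |
| 100% | 10,000 | 8,000 | 80% | 80% |

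With r = 70%, the all-case ratio runs from 14% to 56% as f goes from 20% to 80%; with r = 90%, from 18% to 72%. The two denominators agree only when every patient is febrile at entry.

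**Step 3: the day-3 reading.** Set the listed readings against the 24-hour condition:

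| First reading below 37.3 °C | Next listed reading | Can no recurrence be checked? |
|---|---|---|
| Day 1 | Day 2 | Yes |
| Day 2 | Day 3 | Yes |
| Day 3 | None | No |

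The 7-day time frame adds no temperature reading, and Table 1 names no temperature item at its 7-, 14- and 21-day columns.

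Let s be the share of normalisers whose first normal reading falls on day 3, assumed to be 10% to 40%. Among febrile patients, the confirmed part of the ratio is r × (1 − s). At r = 80% this is 0.80 × 0.90 = 72% down to 0.80 × 0.60 = 48%. The remaining 8 to 32 points are unconfirmed.

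**The case against.** The best defence is that the group in the definition is not spelled out. This is a single cohort without treatment arms, and speaking of a return to normal presupposes a raised starting temperature, so the sponsor may mean febrile patients only. A condensed article may also leave analysis sets to the full protocol. The intention is plausible, but the article does more than stay silent: it fixes the denominator as the total number of cases and nowhere defines a febrile group to which that could refer. Followed as written, it counts afebrile patients.

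Three stronger readings are tempting, and the article does not support them.

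- **Afebrile patients might count as automatic successes**, which would push the ratio up instead of down. The definition requires a drop below 37.3 °C and a return to normal, and a patient who was never above the threshold can do neither.
- **A first normal reading on day 3 might be thought unable to qualify**, making this a 2-day ratio. The condition is that no recurrence is observed, not that a confirming reading is obtained. Patients are also monitored throughout medication (3 to 14 days) and followed for 7 days afterwards. Such a reading is unverified by any listed measurement; it is not disqualified.
- **The ratio might be called uninterpretable.** Temperature is recorded before dosing and daily to day 3, so a meaningful ratio can be recovered from the data already planned.

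It is also fair to say that the outcome is secondary and is to be analysed descriptively.

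**Conclusion.** The point stands in a limited form. The stated denominator includes patients who cannot meet the outcome, so the ratio understates recovery among febrile patients by the factor f. The direction needs no assumed value: for any positive r, any febrile share below 100% pulls the ratio below r. The size does rest on assumptions: 16% to 64% instead of 80% if 80% of febrile patients normalise and 20% to 80% are febrile at entry.

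The day-3 issue is an unevenly verifiable criterion, not an impossible one, and its size depends on an unknown share of late normalisers. The 3-day and 7-day windows contradict each other as written.

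The ADR incidence, the sample size and the risk-factor analysis are untouched. The correction should be made before analysis, but it does not threaten the main purpose of the study.

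**What to change.** 1. Restrict numerator and denominator to patients with a recorded pre-dose temperature of 37.3 °C or higher, the outcome's own threshold, and report how many patients that is.
2. Report first normal readings on days 1 and 2 that remain normal at the next daily reading as confirmed. Show first normal readings on day 3 separately as unconfirmed.
3. Reconcile the 3-day window in the temperature section with the 7-day time frame at the end of the renal-function section.

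The cost is rewording the outcome definition and accepting a smaller denominator: 2,000 to 8,000 of the planned 10,000 under the assumed febrile shares. No new data are needed.

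Two additions that might suggest themselves are not proposed. Interval-censored modelling is a preference that a descriptive outcome does not require. A split by antipyretic use is not supported by the schedule shown: Table 1 ticks concomitant drugs only at 7, 14 and 21 days, which does not establish use within the 3-day window.

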##### Change in Liver Function

We will observe liver function in at least 3000 patients before and after medication. Liver function indexes will include alanine transaminase (ALT) and aspartate transaminase. To observe whether the above liver function indexes appear abnormal after medication, we will use the 2011 International Association for Severe Adverse Reactions–recommended biochemical diagnostic criteria for drug-induced liver injury [31]. Drug-induced liver injury is defined as meeting one of the following conditions:

ALT ≥5× upper limit of normal (ULN);Alkaline phosphatase ≥2×ULN, especially with 5’-nucleotidase or γ-glutamyl transpeptidase elevation, excluding alkaline phosphatase elevation caused by other diseases; orALT ≥3×ULN and total bilirubin ≥2×ULN.

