#### Basic Information Form for Administering PDL

The researchers will record the AE information collected during the study period into the safety monitoring case report form (CRF). All patients will be required to complete CRF A (PDL basic information form). If the monitored patient experiences an ADR or AE during the medication period, the monitor will need to fill out CRF B. We will check the monitoring data; enter, encode, standardize, and clean the data; and then conduct a third-party data inspection. Any discrepancies in the data will be addressed by two data administrators who will resolve them after independently verifying the original CRFs.

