### Interpretation of ADR Causality

In this study, AEs, ADRs, and serious ADRs will be judged according to the *Administrative Measures on Reporting and Monitoring for Adverse Drug Reaction* issued by the Ministry of Health in 2011 [27]. The evaluation of ADRs follows a 3-level decision-making process, comprising initial reporting by clinical practitioners, assessment by the Expert Committee for ADR Monitoring at the surveillance center, and final determination by panel of senior domestic experts. Based on established assessment criteria, the causal relationship between AEs and PDL will be evaluated according to five key parameters: (1) temporal plausibility, (2) consistency with known mechanisms of action or established adverse reaction profiles, (3) positive dechallenge response, (4) positive rechallenge response, and (5) exclusion of alternative explanations. The correlation between AE and PDL will be divided into six grades: positive, probable, possible, possibly unrelated, to be evaluated, and unable to be evaluated. Those judged to be the first three grades will be classified as ADRs, those judged to be “possibly unrelated” will be classified as AEs, and those judged as “to be evaluated” or “unable to be evaluated” should be rejudged in combination with the original monitoring data. We will conduct thorough evaluations to ultimately confirm the incidence of ADRs associated with PDL. This approach helps to minimize potential biases associated with patient self-reporting and variations in medical practices across different centers. The occurrence characteristics and processes of ADRs will be meticulously documented, with particular emphasis on the timing of ADR onset, the implementation time of intervention measures for ADRs, and the termination time of ADRs.

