### Quality Control of ADRs

Each monitoring subcenter will formulate the first-level, quality-control rules and quality-control list according to the content of the monitoring program. The information system of each monitoring unit will be reviewed to ensure that the clinical study data are authentic and traceable. The implementation of the study will adhere to the research protocol and standard operating procedures in order to ensure the authenticity and reliability of the research data. The data collected are presented in Table 1.

**Table 1 table1:** Basic information form for administering Pudilan Xiaoyan oral liquid^a^.

Basic information	Before taking the medicine	After taking the medicine		
		7 days	14 days	21 days
Age	✓			
Sex	✓			
Smoking history	✓			
Occupation	✓			
Expense category^b^	✓			
Pathways to admission	✓			
Drinking alcohol	✓			
Western medicine diagnosis	✓			
Traditional Chinese medicine diagnosis	✓			
Past medical history	✓			
Personal history of allergies	✓			
Allergic manifestation	✓			
Previous other adverse drug reactions or events	✓			
Main drug combination: Western medicine, antibiotics, antipyretic analgesia, proprietary Chinese medicine, or other drugs		✓	✓	✓
Blood routine before and after treatment, white blood cell count, granulocyte, routine urine examination, liver function, renal function, ECG^c^ (test sheet within 30 days before treatment), C-reaction protein, influenza virus detection, pathogen detection, and other tests	✓	✓	✓	✓
Adverse reaction occurrence (yes or no)		✓	✓	✓

^a^Patients are visited and examined before and after taking the medication.

^b^Expense category refers to the classification of expenses, such as out-of-pocket (self-funded) costs, expenses covered by medical insurance, and other payment types. It helps in understanding how different types of expenses are categorized based on their funding source or payment method.

^c^ECG: electrocardiogram.

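### Liver injury is called drug-induced on laboratory thresholds without requiring the plan's own causality grade, so the secondary outcome can contradict the ADR classification of the same patient

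*Protocol article*

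**What the plan says.** The Abstract (Methods) makes the occurrence of drug-induced liver injury part of a secondary outcome. The section Change in Liver Function refers to "biochemical diagnostic criteria for drug-induced liver injury" and then fixes the rule: "Drug-induced liver injury is defined as meeting one of the following conditions". The three conditions are:

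- ALT at least 5×ULN;
- alkaline phosphatase at least 2×ULN, with the qualifier "excluding alkaline phosphatase elevation caused by other diseases";
- ALT at least 3×ULN together with total bilirubin at least 2×ULN.

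On the number tested, the same section says: "We will observe liver function in at least 3000 patients before and after medication".

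The section Interpretation of ADR Causality sets a separate rule for attributing an event to PDL. A three-level assessment weighs five parameters, one of which is that alternative explanations have been excluded. The outcome is one of six grades: "Those judged to be the first three grades will be classified as ADRs". An event graded possibly unrelated stays an AE. The incidence of ADRs is the primary outcome.

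Neither section refers to the other. Table 1 (Quality Control of ADRs) records concomitant treatment: "Main drug combination: Western medicine, antibiotics, antipyretic analgesia, proprietary Chinese medicine, or other drugs".

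**The concern.** The article has two rules for saying that PDL caused something, and they can give different answers for the same patient. The liver rule attaches a causal name to a laboratory value. The ADR rule attaches a causal name only after a judgement that considers other causes.

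This matters because other causes are to be expected. Every patient has an upper respiratory tract infection, and Table 1 anticipates antibiotics, antipyretic analgesics and other drugs. There is no unexposed group from which a background rate of threshold crossing could be read. The Introduction says that the characteristics of PDL-related hepatotoxicity are to be determined, so readers will take the reported rate as an effect of PDL. As defined, the ALT-based part of that rate is liver injury from any cause. A safety study could then publish a causal label that its own expert panel has rejected.

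**Working it through.** **Step 1. Set the two rules side by side.**

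| Route | Threshold | Other causes excluded in the definition? | Causality grade required for the label? |
|---|---|---|---|
| 1 | ALT ≥5×ULN | No | No |
| 2 | Alkaline phosphatase ≥2×ULN | Other diseases yes; co-medication not named | No |
| 3 | ALT ≥3×ULN and total bilirubin ≥2×ULN | No | No |
| ADR rule | None | Yes, as one of five parameters | Yes: positive, probable or possible |

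**Step 2. Follow one patient through both.** A patient on PDL and an antibiotic reaches ALT ≥5×ULN, and the panel grades the event possibly unrelated. Under Change in Liver Function the patient has drug-induced liver injury (route 1). Under Interpretation of ADR Causality the patient has an AE and no ADR. Both statements follow from the text as written.

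**Step 3. The plan's own figure.** The article gives no expected rate of liver injury, so there is none to reproduce. Its one reproducible figure is the 3000 under Sample Size, which is also the minimum number of patients with liver tests. The rule of three gives 3/0.001 = 3000. The exact zero-event calculation, ln(0.05)/ln(1 − 0.001), gives 2995 after rounding up. The figure reproduces, and the point does not depend on it.

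**Step 4. Illustrate the size under assumptions.** Let b be the share of tested patients who meet the definition for reasons other than PDL, and t the true PDL rate. Both are assumed.

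- Expected mislabelled patients = 3000 × b. At b = 0.1% this is 3; at b = 0.5% it is 15.
- Chance of at least one mislabelled patient = 1 − (1 − b)^3000. At b = 0.1% this is 95%; at b = 0.5% it is practically 100%.
- Share of labelled cases not due to PDL = b/(b + t). With t = 0.1% (3 true cases in 3000), this is 50% at b = 0.1% and 83% at b = 0.5%. With t = 0.01% (0.3 true cases expected), it is 91% and 98%.

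At a lower assumed b of 0.05%, the expected number is 1.5 and the chance of at least one is 78%. At a higher b of 1%, the expected number is 30.

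**The case against.** The strongest reply is that this is a descriptive secondary outcome under a heading about change in liver function, and that the article openly calls its criteria biochemical, so a careful reader can see what is counted. That limits the consequence, but the outcome is still named and reported as drug-induced.

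Several stronger readings are tempting, and the documents do not support them.

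- *All three routes rest on thresholds alone.* They do not: the alkaline phosphatase route excludes other diseases.
- *Laboratory events bypass the expert panel.* This would be an inference from silence. The causality section covers AEs in general, and nothing exempts an abnormal liver test. What the text lacks is any rule that the drug-induced label depends on the grade.
- *Silent laboratory injuries will be missing from the primary outcome because no rule makes a threshold value trigger CRF B.* The article says "If the monitored patient experiences an ADR or AE during the medication period, the monitor will need to fill out CRF B", and whether a laboratory value counts as an AE may be settled in the cited regulation or the CRF instructions, which are not shown. A condensed article may leave that to them.
- *Mislabelled cases would move PDL into the occasional frequency class.* Those classes are applied to ADR incidence, which depends on the grade. A case graded possibly unrelated never enters them.
- *The kidney outcome has the same fault.* It is named acute kidney injury, which implies no cause.

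Nor is it a contradiction if a mild PDL-related ALT rise is an ADR without being drug-induced liver injury. An outcome with a severity threshold is expected to leave such cases out.

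**Conclusion.** The point holds for the label. It is clearest for the two ALT-based routes and partial for the alkaline phosphatase route, where only co-medication is left open. It concerns a rule that the article states, not a detail left to a fuller document. The primary ADR incidence is not itself altered; the secondary drug-induced count can be too high and can disagree with it.

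How far cannot be derived, because the documents give no background rate of threshold crossing. The range of 3 to 15 mislabelled patients in 3000 rests wholly on the assumed 0.1% to 0.5%. It also assumes that the definition is applied as written, with no unstated causality check before a case is counted.

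**What to change.** Amend Change in Liver Function in three respects:

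1. Report every patient who meets a threshold as having biochemical liver injury from any cause.
2. Send each such patient through the assessment in Interpretation of ADR Causality.
3. Use the term drug-induced (PDL-related) liver injury only for those graded positive, probable or possible.

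Every case in the third group is then also an ADR, so the liver count agrees with the primary outcome. Background cases drop out of it to the extent that the grading is accurate; those graded possible in error would remain.

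The thresholds, the tests and patient care stay as they are. The cost is a few sentences and a few more cases for the existing panel (3 to 15 background cases per 3000 tested under the assumption above, plus any true ones). The drug-induced figure may fall, while the all-cause figure keeps every crossing visible.
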